## 3 IRB Review History

This protocol was initially approved on September 16, 2013. It has been assigned IRB#450072.

## 4 Objectives

**AIM 1. To characterize stool microbiotal composition and immune markers after administration of a probiotic with and without a prebiotic in children with autism.**

Hypothesis 1.1: Synbiotic administration of *Bifidobacterium infantis* (probiotic) and bovine milk oligosaccharides (prebiotic) will alter the composition of stool microbiota, with greater increases in commensal actinobacteria (including *B. infantis*) and decreases in pathogenic proteobacteria than *B. infantis* alone.

Hypothesis 1.2: Synbiotic administration of *Bifidobacterium infantis* and bovine milk oligosaccharides will alter serum immune (cytokine, immunoglobulin) measures.

**AIM 2 (exploratory). To determine tolerability of *Bifidobacterium infantis* and bovine milk oligosaccharides in children with autism.**

Hypothesis 2.1: *Bifidobacterium infantis* and bovine milk oligosaccharides will be well tolerated in children with autism, as measured by gastrointestinal and behavioral symptoms.

## 5 Background

Gastrointestinal (GI) symptoms (most commonly, constipation and diarrhea) are frequently reported in autism (AU)(Buie, Campbell et al. 2010), and biological differences in this subgroup, specifically the bacterial microbiome of the gut (Finegold, Molitoris et al. 2002), may suggest links between the brain and gut via the immune system. Abnormalities in immune function and cytokines have been reported in some children with autism ([name], Anthony et al. 2004) and this may both lead to GI symptoms and be influenced by substances presenting to the immune system from the gut. Immune markers, such as cytokines, can affect the central nervous system through glial cells and alterations in neurotransmitters (Merali, Lacosta et al. 1997). Probiotics (beneficial living organisms) are widely used dietary supplements that are one of the most frequently encouraged complementary alternative treatments by general pediatricians and family practice providers

[figure not shown]

A pilot study examining the microbiotal composition in children with autism after use of *Bifidobacterium infantis* and milk oligosaccharides.

(Golnik and Ireland 2009). Probiotics can stimulate immunity and modulate intestinal microflora. *Bifidobacterium infantis* is highly present in the intestines of healthy breast-fed infants and decreased in the digestive tract of some children with autism (Finegold, Dowd et al. 2010). It has been beneficial in gastrointestinal disorders such as irritable bowel syndrome and necrotizing enterocolitis (Alfaleh and Bassler 2008). Oligosaccharides are sugars that serve as “prebiotics,” stimulating the activity of *B. infantis*. **Our primary goal is to study stool microbiotal composition after the administration of a synbiotic, which is a probiotic (*Bifidobacterium infantis*) in combination with a prebiotic (BMO: bovine milk oligosaccharides).** We will compare microbial composition from baseline in order to determine the effect of the synbiotic. In this pilot study, we also explore if the synbiotic results in greater changes compared with the administration of the prebiotic alone (BMO obtained from bovine colostrum). Serum immune markers will be collected to reflect changes in the intestinal microbiome. Tolerability will be assessed through behavioral measures, including GI symptoms, clinician assessment, and parent questionnaires to provide further support for microbiotal changes.

Probiotics are non-pathological organisms with potentially beneficial effects via immune modulation (Gill and Prasad 2008, Paineau, Carcano et al. 2008) and/or competitive inhibition of other species. Common probiotics include bacteria such as lactobacilli, lactococci, and bifidobacteria and they are frequently present in yogurt and fermented foods (i.e. sauerkraut). Lactobacilli and bifidobacteria are normally present in the GI system soon after birth (Borriello, Hammes et al. 2003). They are considered to have little or no pathologic potential (Mäkeläinen, Tahvonen et al. 2003) and are “Generally Recognized as Safe (GRAS)” (GRAS; <http://goo.gl/ljzVO>) by the U.S. Food and Drug Administration and have a “Qualified Presumption of Safety (QPS).” Side effects are uncommon and usually mild, including constipation, increased thirst, bloating and gas (McFarland 2006). A workgroup of experts in clinical practice, microbiology, intestinal microecology, pathogenicity, nutrition, toxicology, and public health reported that probiotics are suitable and well tolerated for infants and children (Borriello, Hammes et al. 2003).

There are documented abnormalities in the composition of the microbiota, immune function, and intestinal permeability in individuals with autism. Abnormal microbiota composition in autism includes greater representation of toxin-producing *Clostridium* species (Finegold, Molitoris et al. 2002) and decreased *Bifidobacterium* species (Finegold, Dowd et al. 2010, Adams, Audhya et al. 2011). Alteration of the intestinal microbiotal imbalance can alter gut motility and secretion (Critchfield, van Hemert et al. 2011). In addition, reports of elevated levels of antibodies against dietary peptides (de Magistris et al. 2013) and gut peptidases (Vojdani et al. 2004) as well as low digestive enzyme activity (Horvath et al. 1999) and elevated levels of urinary peptides of dietary origin (Reichelt et al. 2003, Reichelt et al. 2009) in some children with autism suggest an impaired capacity for protein digestion. Therefore, exploratory analysis of markers of intestinal permeability (zonulin) (Fasano 2011), pancreatic insufficiency (elastase-1) (Naruse et al. 2006) and microbial putrefaction (protein fermentation metabolites such as ammonia, phenols and sulfides) as well as protein digestion products (peptides) will be assessed in the feces, urine and plasma.

[figure not shown]

A pilot study examining the microbiotal composition in children with autism after use of *Bifidobacterium infantis* and milk oligosaccharides.

Immune dysfunction and atypical pro-inflammatory cytokine profiles have been documented in autism ([name], Anthony et al. 2003, [name], Anthony et al. 2004, [name] and Wakefield 2006) and these are potential mediators between the GI and nervous systems. Cytokines can modulate intestinal epithelial barrier function (“leaky gut”), which is seen in some individuals with autism (D'Eufemia, Celli et al. 1996, Horvath and Perman 2002) and can affect neural signaling through glial cells and/or neurotransmitter metabolism (Merali, Lacosta et al. 1997). Increased gut permeability can also allow for the presentation of antigenic material to trigger an immune response. Both *B. infantis* and Bovine Milk Oligosaccharides (BMO) have been shown to be safe and well tolerated in adults and premature infants without complications (Parente, Cucino et al. 2003, Eiwegger, Stahl et al. 2004, LoCascio, Ninonuevo et al. 2007, Sela, Chapman et al. 2008, German, Freeman et al. 2009, Marcobal, Barboza et al. 2010, Sela, Li et al. 2011, Zivkovic, German et al. 2011). A UCDMC study in premature infants demonstrated that probiotics with fructo-oligosaccharide (FOS) were well tolerated without side effects noted. Currently, the UCDMC NICU is conducting a trial of bifidobacteria and oligosaccharides in premature infants and there is an ongoing study of milk oligosaccharides in healthy adults at the UC Davis Foods for Health Institute.

For description of and previous experience with the product: please see Appendix 1.

## 6 Inclusion and Exclusion Criteria

### Inclusion criteria:

Participants ages 2-11 years of age with a confirmed diagnosis of autism/autism spectrum disorder (ASD) based on the ADI-R and/or ADOS will be eligible. The diagnosis of autism/ASD from another source deemed reliable may also be used. Participants must report the presence of diarrhea and/or constipation based on screening questions from the CHARGE GI questionnaire and a subset of questions from the Questionnaire on Pediatric Gastrointestinal Symptoms-Rome III Version (QPGS-RIII). A reliable caregiver must be available to accompany the child to all visits and oversee proper administration of the synbiotic. Families must agree to not change any interventions during the course of the trial.

Participants meeting all of these criteria may be enrolled provided that they do not meet any of the exclusionary criteria below.

### Exclusion criteria:

Participants will be excluded if they have a reliable history of milk protein or other documented food allergy. Exclusionary medical conditions include, but are not limited to: compromised immunity, GI conditions (inflammatory bowel disease, celiac disease, short gut, etc.), systemic steroid, antifungal, or antibiotic use within the past month, failure to thrive, and individuals on medically prescribed diets or supplements (including probiotic use within the past month) other than a standard multivitamin. Children with other medical conditions, such as uncontrolled seizure disorder, genetic disorders (fragile X syndrome, tuberous sclerosis, etc), liver/pancreatic disease, cystic fibrosis, or other serious medical condition determined by the study

[figure not shown]

A pilot study examining the microbial composition in children with autism after use of *Bifidobacterium infantis* and milk oligosaccharides.

physician will also be excluded. Medications that may interfere with intestinal mobility or microbiota composition will also not be allowed. Participants with a full scale IQ <40 will be excluded. A prior IQ score from a source deemed reliable may be used. (For example, from a licensed physician, psychologist, psychometrist or other qualified professional.)

Participants will be pre-screened for eligibility in this study by phone using the study's oral consent form. Oral consent forms will be reviewed by [name] before for final approval for enrollment in the study.

## **7 Study-Wide Number of Subjects**

We intend to enroll twenty subjects in hopes of having ten subjects complete the protocol.

## **8 Study-Wide Recruitment Methods**

Twenty children with autism/ASD and irregular bowel movements ages 2-11 years of age will be recruited for this study. Recruitment strategies will include solicitation of families who have participated in [name] Speaks study "Defining the Underlying Biology of Gastrointestinal Dysfunction in Autism," all of whom participated in the CHARGE (Childhood Autism Risks from Genetics and the Environment) study and received autism diagnostic assessments. Additionally, only families that indicated a desire to be contacted for future studies will be solicited.

We will also contact families who have participated in prior research at the MIND Institute and who have agreed to be contacted for future studies through the MIND Research Volunteer Registry. These families will initially be contacted either by phone or email and asked to participate in an oral consent questionnaire to evaluate eligibility. A flyer explaining the study will also be available to families in clinic. Upon completion of the questionnaire, and approval from [name], the participant and his or her family will be invited to complete a screening visit for the study.

Upon successful completion of the screening visit, participants will be asked to begin the trial.

## **9 Study Timelines**

Screening and enrollment will begin upon IRB approval of this protocol and associated documents. Enrollment will continue for approximately two months in order to reach the full enrollment.

Each participant will be involved in this trial for a period of twelve weeks. This will include four visits to the UC Davis MIND Institute and two phone call checks. See Table 1 listed on page 7 for

[figure not shown]

A pilot study examining the microbiotal composition in children with autism after use of *Bifidobacterium infantis* and milk oligosaccharides.

procedures Involved.

[figure not shown]

Figure 1: Study diagram

Participants will be active in this trial until about February, at which point the final participant will have completed the trial period.

Data analysis of data collected during the trial period of each participant will be analyzed after the final participant has completed the trial, which is expected to be about March 2014.

## 10 Study Endpoints

The primary endpoint will be change in intestinal microbiotal composition. Secondary endpoints will include change in serum immune markers, fecal and plasma zonulin, fecal elastase-1, fecal and urinary protein/peptide profiles, and fecal and urinary microbial putrefaction metabolites.

Tolerability will be monitored through GI questionnaires, behavioral questionnaires, and clinician assessment.

## 11 Procedures Involved

This pilot study is a randomized, controlled trial of a synbiotic (BMO + *B. infantis*) vs. BMO alone.

### Synbiotic/BMO only administration

Each participant will be randomized by the IDS pharmacy to receive either the synbiotic first or the BMO first in a cross-over study design. This is a double blind study in that both participants and study personnel will not be aware of which treatment arm the participant will receive first. The study supplement will be dispensed in identically packaged pouches. The study will last 12 weeks, including 5 weeks of BMO use, 5 weeks of the synbiotic, and a two-week washout period in between.

A pilot study examining the microbial composition in children with autism after use of *Bifidobacterium infantis* and milk oligosaccharides.

The synbiotic and the BMO will be given once a day. Each synbiotic dose will be **100 mg of *B. infantis*, or 10 Billion CFU ( $1 \times 10^{10}$ )**, delivered once a day with **0.15 g/pound body weight per day of BMO**. The **BMO only arm** will be the identical dose of 0.15 g/pound body weight/day BMO given orally. The synbiotic or BMO will be a powder the parent can deliver in many different recipes including any cold milk-based liquid, ice-cream or pudding. Parents will be provided an individualized recipe booklet that provides dosing strategies and instructions as well as a magic bullet blender to facilitate supplement incorporation into food items. Parents will also be instructed to store the study drug in the freezer and to ensure the child consumes the entire supplement dose within 20 minutes.

### **Stool Collection**

Baseline stool samples will be collected within 48 hours prior to the first dose of synbiotic. Subsequent samples will be taken after completing the first study arm at week 5, after completing the washout period at week 7, and after completing the second arm of the study at week 12.

Families will be given a kit including a styrofoam container with an ice pack, and a sterile tongue blade. Stool samples will be collected at home by the parent prior to their study visit into a sterile specimen container using a sterile tongue blade and kept cold in either a styrofoam transport container with ice pack or their home freezer until the visit.

Stool samples will be analyzed for microbial composition, microbial metabolites, peptide profile, intestinal permeability (zonulin), and pancreatic insufficiency (elastase-1).

### **Urine Collection**

Urine will be collected at each visit for exploratory analysis to characterize microbial metabolites as a biomarker of intestinal microbiota as well as peptide profiling. Parents or caregivers will be asked to assist in collecting a first morning void. Children who are not developmentally able to void at will shall be given the option to use a bag for collection. Upon collection, parents or caregivers will be asked to store the sample in either their home freezer or in the provided styrofoam transport container with ice pack. Samples will be stored long term at -80°C until analyzed by mass spectroscopy and NMR for metabolomics and peptidomics.

### **Blood Draw**

Blood will be drawn from patients at each visit. Blood will be drawn on site at the UC Davis MIND Institute by a study physician or certified phlebotomist experienced in working with children with neurodevelopmental disorders. Up to 28 mL of blood will be collected at each draw. . Cytokines will be measured by Luminex technology in the [name] laboratory to determine profiles of pro-inflammatory (IFNg, IL-1, IL-6, IL-13 and TNFa) cytokines and anti-inflammatory (IL-10 and TGFb1) cytokines. Following the synbiotic, we expect to see increases in anti-inflammatory cytokines. We will also determine immunoglobulin levels (IgA, IgG and IgM) by ELISA. In previous

[figure not shown]

A pilot study examining the microbiotal composition in children with autism after use of *Bifidobacterium infantis* and milk oligosaccharides.

studies we have seen that immunoglobulin levels are decreased in children with autism; following synbiotic administration, we expect to see levels increase to those seen in typical developing children of the same age. The blood draw will also include a CBC (Complete Blood Count) for safety as well as plasma biomarkers of microbial metabolites and intestinal permeability (zonulin).

**Table 1. Study visits, assessments, and procedures.**

|                            | Week 0                                    | Week 2/3 | Week 5  | Week 7  | Week 9/10 | Week 12 |
|----------------------------|-------------------------------------------|----------|---------|---------|-----------|---------|
| Assessment                 | Baseline Visit                            | Call 2   | Visit 3 | Visit 4 | Call 2    | Visit 4 |
| ADOS/ADI-R                 | Obtained Previously From A Reliable Rater |          |         |         |           |         |
| IQ / Developmental Testing | Obtained Previously From A Reliable Rater |          |         |         |           |         |
| ABAS-II                    | X                                         |          |         |         |           |         |
| Physical Exam/ Vitals      | X                                         |          | X       | X       |           | X       |
| Adverse Events             | X                                         | X        | X       | X       | X         | X       |
| GI Questionnaires          | X                                         |          | X       | X       |           | X       |
| ABC                        | X                                         |          | X       | X       |           | X       |
| RBS-R                      | X                                         |          | X       | X       |           | X       |
| Stool Sample               | X                                         |          | X       | X       |           | X       |
| Urine Sample               | X                                         |          | X       | X       |           | X       |
| Blood Draw                 | X                                         |          | X       | X       |           | X       |

### **Adaptive Behavior Assessment System – Second Edition (ABAS-2)**

The ABAS-2 is composed of three domains, including conceptual, social, and practical. The domains are sub-divided into ten different skills areas that generate a norm-referenced standard score. The ABAS-II has been previously approved by the IRB as part of the MIND Institute Protocol Repository (MIPR, IRB#200513093).

### **Medical History and Physical Exam**

[figure not shown]

A pilot study examining the microbiotal composition in children with autism after use of *Bifidobacterium infantis* and milk oligosaccharides.

During visits to the UC Davis MIND Institute, participants will undergo a physical exam and answer questions about their medical history. These appointments will include a review of adverse events for returning participants. Adverse events will also be queried via phone call throughout the study.

### **GI questionnaires**

#### **CHARGE Gastrointestinal History Questionnaire**

The GI History includes 10 Likert scale items (0=never; 1=rarely; 2=sometimes; 3=frequently; 4=always) for each current and past (last 3 months) gastrointestinal symptom (abdominal pain, gaseousness/bloating, diarrhea, constipation, pain on stooling, vomiting, sensitivity to foods, difficulty swallowing, blood in stool and blood in vomit). The CHARGE GI History Questionnaire is included in this submission.

#### **Questionnaire on Pediatric Gastrointestinal Symptoms (QPGS-RIII)**

The QPGS-Rome III, is a parent-report measure of gastrointestinal symptoms scored on a 5-point scale and assesses functional gastrointestinal disorders based on the Rome III criteria. Only a specific subset of the questions on the QPGS-RIII will be used as part of this study, as conditions of interest for this study include functional diarrhea, functional constipation, and irritable bowel syndrome. This subset of questions can be found in the Oral Consent form, and the same questions will be used throughout the study as a measure of gastrointestinal function.

#### **Aberrant Behavior Checklist (ABC)**

The ABC is a parental survey consisting of 58 questions designed to measure the severity of autism-associated behaviors, including irritability, lethargy, stereotypy, hyperactivity and inappropriate speech. The irritability subscale includes self-injurious and aggressive behavior. The total score range within the ABC is 0–174, with higher scores indicating more severely affected behavior. The ABC has been previously approved by the IRB as it is part of the MIND Institute Protocol Repository (MIPR, IRB # 200513093).

#### **Repetitive Behavior Scale-Revised (RBS-R)**

The RBS-R is a 44-item self-report questionnaire that is used to measure the breadth of repetitive behavior in children, adolescents, and adults with Autism Spectrum disorders. The RBS-R consists of six subscales including: Stereotyped Behavior, Self-injurious Behavior, Compulsive Behavior, Routine Behavior, Sameness Behavior, and Restricted Behavior. Behaviors are rated on a 4-point scale: 0-Behavior does not occur, 1-Behavior occurs and is a mild problem, 2-Behavior occurs and is a moderate problem, 3-Behavior occurs and is a severe problem. The RBS-R has been previously approved by the IRB as it is part of the MIND Institute Protocol Repository (MIPR, IRB # 200513093).

#### **Bristol Stool Form Scale**

The Bristol Stool Form Scale is a seven point visual scale used to classify stool consistency. Parents will be asked to keep track of their child's bowel movements throughout their participation

[figure not shown]

A pilot study examining the microbiotal composition in children with autism after use of *Bifidobacterium infantis* and milk oligosaccharides.

in this study (as asked on a stool log), and to record each stools' consistency as described by this scale.

## 12 Data and Specimen Banking

Each sample will be coded by a unique numerical identifier.

Biological samples (blood, urine and stool) will be kept for a maximum of ten years and will be destroyed in accordance with protocols in place for biological samples. Stool will be autoclaved prior to disposal. Urine will be neutralized with bleach to make a 10% bleach solution that will incubate at room temp for 30 minutes prior to pouring down the sink with cold running water.

Blood: Blood will be drawn at four points throughout the study with a total blood draw volume of up to 28 mL at each draw. Serum samples will be delivered daily to [name] lab located in the Wet Lab at the MIND Institute.

Urine: Urine samples will be collected at four points throughout the study. Samples will be stored at -80°C until analyzed.

Stool: Patient's caregivers will be asked to collect a stool sample just prior to each visit requiring such a sample. Caregivers will be given a kit (a small styrofoam container with a cold pack, sterile tongue blade, and a sterile specimen container). Caregivers will be asked to keep the cold pack in their home freezer until a sample is obtained (generally no more than 36 hours prior to a scheduled visit, 48 hours at the most). The sample will be stored in the styrofoam container with the cold pack until it is brought in during their next visit. Upon obtaining the stool sample from the caregivers, the samples will be frozen at -20°C and transported to [name] lab weekly where samples will be kept frozen at -80°C.

Stool samples will be picked up weekly by a member of [name] lab, or study personnel from the MIND will deliver the specimens to [name] lab on ice. In the [name] lab, stool will be extracted and 16S rDNA-based PCR primers for total bacteria and total bifidobacteria will be used to determine the percentage of bifidobacteria present. Species specific bifidobacteria primers will then be used to determine whether the administered strain is the dominant stool strain (groups 3-8) and whether the administered oligosaccharide stimulates a specific strain (groups 1, 2, and 5-8).

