### [name] Lab

[name] has a well-equipped anaerobic microbiology lab and has previously evaluated a wide variety of bifidobacteria species including the ability of specific micro-organisms to grow in oligosaccharide medium. [name] lab also has thermocycler equipment to quantify bifidobacteria. The [name] laboratory is in the new Robert Mondavi Institute for Wine and Food Science at UC Davis. This includes a ~1000 square-foot lab equipped for all proposed microbiological and biochemical work. The laboratory is equipped with a specially designed Coy anaerobic chamber with incubator, a BioTek PowerWave 340 plate reader and all the necessary tools to perform the prebiotic screening and microbial BMO-functionality assays. Existing equipment that will be used in this project are: incubators, 2 anaerobic hoods, shakers, biosafety hood, ovens, UV-Vis spectrophotometers, electrophoresis apparatus, gel documentation equipment, refrigerators, freezers, cell disrupters, microscopes, table top centrifuge, microcentrifuges, high-speed centrifuge, several -80C freezers, 2 real time thermocyclers, and 2 microtiter plate readers for bacterial growth studies. The laboratory is equipped with five Macintosh computers, two Pentium PC computers, and several common printers.

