## 26 Local Number of Subjects

This study intends to have 10 subjects complete the study protocol, and we expect to enroll up to twenty subjects to account for screening failures and early terminations.

**Power Analysis:** The proposed two-period crossover study design with baseline and follow-up measurements for each period will enable each child to serve as their own control for purposes of quantifying the effects of synbiotic on microbiotic outcomes. The effect size parameter of interest will be the mean within-child between-period (synbiotic vs. prebiotic) difference in within-period change (from baseline to follow-up). With an analysis of ten children, the proposed study design will allow us to estimate the parameter of interest with sufficient precision that the margins of error (i.e. halfwidths of 95% confidence intervals) will be 1.4 root mean square error (rmse) wide. In addition, the study will have **80% power** to detect differences of magnitude 1.94 rmse, under two-sided testing (with  $\alpha=5\%$ ) of the null hypothesis that the effect size is 0. The rmse is the square root of the residual error variance component. The residual error variance component is equal to  $(1 - R) * V$ , where R is the within-child correlation and V is the total variance of the outcome distribution. To our knowledge, no estimates are available of the within-child correlation for the proposed outcomes in this clinical population. (Indeed, this is one of the knowledge gaps that the pilot study will aim to fill.) However, [name] lab have measured similar bifidogenic response in infants, for whom the within-infant correlations have ranged as high as 40%. Although it is plausible

[figure not shown]

A pilot study examining the microbiotal composition in children with autism after use of *Bifidobacterium infantis* and milk oligosaccharides.

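### The only readout described for the administered *B. infantis* is a yes/no dominance call with no threshold, which does not match a hypothesis and a power calculation about the size of a change

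*Protocol*

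**What the plan says.** Section 12 (Data and Specimen Banking) describes two PCR steps on stool. For the genus the output is a quantity: "16S rDNA-based PCR primers for total bacteria and total bifidobacteria will be used to determine the percentage of bifidobacteria present". For the administered organism it is a question with a yes/no answer: "Species specific bifidobacteria primers will then be used to determine whether the administered strain is the dominant stool strain". No threshold for dominance is given. The same sentence assigns this question to groups 3 to 8, and a second question, whether the oligosaccharide stimulates a particular strain, to groups 1, 2 and 5 to 8. Section 11 describes one randomised crossover of synbiotic against BMO alone, with no such groups.

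Three other places bear on the scale of the readout:

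- Section 4, Hypothesis 1.1, predicts "greater increases in commensal actinobacteria (including" *B. infantis*) on the synbiotic.
- Section 10 states: "The primary endpoint will be change in intestinal microbiotal composition".
- Section 26 defines the effect of interest as the mean within-child, between-period "difference in within-period change (from baseline to follow-up").

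On capability, Section 22 says that the microbiology laboratory "also has thermocycler equipment to quantify bifidobacteria" and lists real-time thermocyclers.

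**The concern.** Under Section 11 the BMO dose is identical in both periods, so *B. infantis* is the only component that differs between the two products. Its abundance in stool is the most direct measure of what the randomisation changes. The genus percentage is not a full substitute: BMO may itself raise other bifidobacteria, and the genus share could stay flat if *B. infantis* displaced them.

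A yes/no call discards the size of the change. A child whose *B. infantis* rises manyfold without becoming dominant is scored like a child with no rise, and a child in whom it is already dominant at period baseline cannot show an increase. With ten children, a paired binary comparison also leaves few discordant pairs. Section 26 says that the pilot should help fill the gap in knowledge of within-child correlations; a dominance call cannot supply one for *B. infantis* abundance.

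**Working it through.** **Inputs from Section 26:** 10 children analysed; two-sided alpha 5%; detectable difference 1.94 rmse at 80% power; half-width of the 95% interval 1.4 rmse; residual variance (1 − R)V; R from 0.4 (base case) to 0.7.

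**Step 1. Reproduce the plan's figures.** A difference of two changes combines four measurements, so its SD per child is √4 = 2 rmse and SE = 2/√10 = 0.632 rmse.

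- With t on 10 df (inferred, not stated), the half-width is 2.228 × 0.632 = 1.41 rmse.
- The detectable difference is (2.228 + 0.842) × 0.632 = 1.94 rmse.

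Both match. Noncentral-t power at 1.94 rmse is 77.9% on 9 df and 78.9% on 10 df. In rmse units this does not depend on R.

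**Step 2. Suppose instead that dominance at the end of each period were compared between products.** Assume normal abundance on the analysis scale, equal variances, correlation R between the two end-of-period values, no carryover, and a shift of 1.94 rmse. In rmse units the SD of a single value is 1/√(1 − R). Put the cut midway between the two means, at 0.97 rmse; this was the best cut in a search over thresholds.

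| | R = 0.4 | R = 0.7 |
|---|---|---|
| SD of one value (rmse) | 1.29 | 1.83 |
| Dominant on synbiotic | 77% | 70% |
| Dominant on BMO | 23% | 30% |
| Dominant on synbiotic only | 0.567 | 0.418 |
| Dominant on BMO only | 0.019 | 0.013 |
| Expected discordant pairs of 10 | 5.9 | 4.3 |

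**Step 3. Exact two-sided McNemar test.** Five discordant pairs all in one direction give p = 2 × 0.5⁵ = 0.0625, which is not significant. Rejection needs 6, 7 or 8 discordant pairs with none in the minority direction, or 9 or 10 with at most one. Summing the multinomial probabilities over that region gives:

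- R = 0.4: power 48%
- R = 0.7: power 18%

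**Step 4. How far this depends on the assumptions.**

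- *Cut.* At R = 0.4, cuts about 1 rmse off centre give 21% to 24%.
- *Test.* The mid-p McNemar test gives 69% at R = 0.4 and 38% at R = 0.7.
- *Comparator.* The uncut end-of-period value, analysed by paired t test, has SE = √(2/10) = 0.447 rmse and 97% power. At R = 0.4 the binary readout therefore has 0.48/0.97 = 0.50 of the power of the uncut value, but 0.48/0.78 = 0.62 of that of the planned contrast.
- *Effect size.* At 3 rmse with the midpoint cut, the binary readout reaches 91% (R = 0.4) or 60% (R = 0.7), against 99% for the planned contrast.
- *No dominance on BMO at all (an assumption).* Exact power is 38%, 63%, 85% and 97% if 50%, 60%, 70% and 80% of children are dominant on synbiotic.

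**The case against.** The strongest reply is that the protocol plans no binary analysis. The sentence is a laboratory description in a specimen section and names no endpoint, test or threshold. The endpoint, hypothesis and power sections all point to change on a continuous scale, and a statistical analysis plan may settle how species-level PCR output is scaled. Its group numbers do not fit this trial, so its literal wording is weak evidence of intent. Deciding which strain is dominant also requires relative amounts, and the sentence does not say that those are discarded.

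Most of this stands. A reader might infer that the primary analysis is binary; the documents do not show that, and the McNemar test above is an illustration rather than the plan's method. A reader might also infer that dichotomising always costs at least half the power. Step 4 shows otherwise: one half applies against the uncut end-of-period value at R = 0.4 with the exact test, the ratio to the planned contrast is about 0.6, and at R = 0.4 the gap nearly closes for large effects. Large effects are plausible, because the organism is given in only one period. Nor do the documents say that the laboratory quantifies *B. infantis* itself. Sections 12 and 22 speak of bifidobacteria as a genus, and species-level quantification is inferred from the species-specific primers and the real-time equipment.

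What the reply does not remove is that the protocol states a readout for the administered organism, and the one it states cannot yield the quantity that Hypothesis 1.1 and Section 26 are about.

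**Conclusion.** The point holds as a mismatch in the stated readout. Section 12 gives the genus a percentage but the administered organism only a yes/no call without a threshold, in a sentence tied to groups that this crossover does not contain. That does not fit Hypothesis 1.1 or the effect parameter in Section 26.

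The size is conditional. If dominance were used for the treatment comparison at 1.94 rmse with ten children, power would be about 48% (R = 0.4) or 18% (R = 0.7) with an exact McNemar test at the midpoint cut, against about 78% for the planned contrast. This assumes normal abundance on the analysis scale, equal variances and no carryover. The protocol gives no dominance rate or cut, so no single figure for the loss can be claimed. It is an inexpensive improvement worth making, not a demonstrated flaw in the primary analysis.

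**What to change.** Reword the sentence in Section 12 along these lines: *Species-specific primers will be used in real-time PCR to quantify B. infantis in each stool sample, for example as log abundance or as a share of total bacteria or total bifidobacteria. Its change within each period will be analysed on the continuous scale with the synbiotic-versus-BMO crossover contrast of Section 26. Whether the administered strain is dominant will be reported descriptively only.* Choose one scale in advance, and delete the references to groups 1 to 8.

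No extra samples or visits are needed; the stools, primers and type of equipment are already in the protocol. The added work is a standard curve and a stated rule for values below the quantification limit, which may be common in the BMO-only period.
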